#### CB ablation

2.6.2

The detailed procedure has been described elsewhere.^16^ The fourth‐generation CB will be used in the CB ablation group. In brief, an 8.5‐F sheath (SL0, Abbott) will be exchanged for a 15‐F steerable sheath (FlexCath, Medtronic) after the transseptal puncture, and a 28‐mm CB will be introduced into the LA through the sheath. The CB will be inflated proximal to each PV and pushed gently to seal the antral aspect of the PV through a circular catheter (Achieve). Injection of contrast medium will be performed to confirm the relative position of the CB and PV antrum. A 180 s or time to isolation plus a 120‐s freeze cycle will be performed at each PV.^16^, ^17^ When the initial freezing fails to isolate the PV, the CB will be repositioned, and a second freezing cycle will be applied. When the CB ablation cannot achieve the PVI, additional focal ablation will be performed with a Freezor Max (Medtronic) or RF catheter.

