### Statistical analysis

2.11

For the primary endpoint, safety analyses will be performed based on the intention‐to‐treat principle. A per‐protocol basis analysis will also be performed as a supplemental analysis. When noninferiority is demonstrated on the primary endpoint, the superiority hypothesis will also be evaluated. An asymptotic method based on the normal distribution will be used to compare the rate of SCEs by brain MRI 1–3 days after CA of AF.

Other categorical variables will be presented as absolute and relative frequencies and compared using a chi‐square test or Fisher's exact test. Continuous variables will be presented as the mean ± standard deviation for normally distributed data or median with the interquartile range (25th–75th percentiles) for skewed data and analyzed with the Student's *t*‐test or Wilcoxon rank‐sum test, as appropriate. If RF catheters are used in the CB ablation group for touch‐ups, we plan to carry out analyses that include both patients with touch‐ups and that excludes those without touch‐ups, respectively.

A *p* < .05 will be considered statistically significant. Logistic regression analyses and multivariable Cox regression analyses will be performed to investigate the predictors associated with clinical outcomes. Statistical analysis will be performed using up‐to‐date versions of the Stata software (StataCorp). The patient demographic data and outcomes of the CA in each group will be collected descriptively as presented in Tables 1 and 2. A detailed plan for the interim analysis and final analysis will be prespecified in the statistical analysis plan, which will be prepared and finalized before the database lock.

**Table 1 clc23949-tbl-0001:** Patient characteristics at baseline

Age, years, *n* (%)
Female sex, *n* (%)
Height, cm
Weight, kg
Body mass index
AF type
Blood pressure, mmHg
Heart rate, /min
Congestive heart failure, n (%)
Hypertension, *n* (%)
Diabetes mellitus, *n* (%)
Stroke and/or transient ischemic attack, *n* (%)
Vascular disease, *n* (%)
Structural heart disease, *n* (%)
Coronary artery disease
Valvular heat disease
Dilated cardiomyopathy
Hypertrophic cardiomyopathy
Others
Post‐open heart surgery
NYHA class
Bleeding history or predisposition
Labile INR, *n* (%)
Concomitant aspiring or nonsteroidal anti‐inflammatory drugs
Excess alcohol use
CHADS_2_ score
CHA_2_DS_2_‐VASc score
HAS‐BLED score
Transthoracic echocardiographic data
LV ejection fraction, %
LV end‐diastolic diameter

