LV end‐systolic diameter
LA dimension, mm (%)
LA volume, ml
Transmitral flow
Mitral valve regurgitation
Tricuspid valve regurgitation
Transesophageal echocardiographic data
LA appendage inflow velocity
LA appendage outflow velocity
Spontaneous echo contrast
Cardiac implantable electronic device, n (%)
Pacemaker, *n* (%)
ICD, *n* (%)
CRT‐P, *n* (%)
CRT‐D, *n* (%)
Type and dose of anticoagulant
History of antiarrhythmic drug use, *n* (%)
Disopyramide, *n* (%)
Cibenzoline, *n* (%)
Aprindine, *n* (%)
Pilsicainide, *n* (%)
Flecainide, *n* (%)
Propafenone, *n* (%)
Bepridil, *n* (%)
Sotalol, *n* (%)
Amiodarone, *n* (%)
Verapamil, *n* (%)
Beta‐blocker, *n* (%)
Digitalis, *n* (%)
Others, *n* (%)
Laboratory data

Abbreviations: AF, atrial fibrillation; CRT‐D, cardiac resynchronization therapy defibrillator; CRT‐P, cardiac resynchronization therapy pacemaker; ICD, implantable cardioverter defibrillator; INR, international normalized ratio; LA, left atrium; LV, left ventricle; NYHA, New York Heart Association.

**Table 2 clc23949-tbl-0002:** The CA procedure and complications

Procedure time (groin puncture to catheter extraction), min
LA dwell time, min
Fluoroscopic time, min
General anesthesia, *n* (%)
For CB ablation
Total freeze cycles, *n*
Total freeze time, s
The need for touch‐up ablation, *n*
Reinsertion of withdrawn CB
Mapping of LA before ablation
Mapping of LA after ablation
For RF ablation
Type of ablation catheter
Total RF application time, s
Power, W
Duration at each application site, s
Ablation index for CARTO, lesion index for NavX
Other adjunctive ablation, *n* (%)
Use of 3D mapping system, *n* (%)
Low voltage zone ≥10% of LA surface
Electrical cardioversion during CA procedure, *n* (%)
Number of cardioversion during CA procedure, *n* (%)
Initial heparin dose, U
Time required to reach target ACT of >300, min
Mean ACT value during CA procedure
Total heparin dose, U
Use of protamine at the end of CA procedure, n (%)
Transcarotid echography during CA procedure
Microembolic signals, *n*
High‐intensity transient signals (microparticles), n
Microbubbles, *n*
Brain MRI
Silent cerebral events, *n* (%)
Location and number of silent cerebral events
Silent cerebral lesions, *n* (%)
Location and number of silent cerebral lesions
Microbleeds, *n* (%)
Location and number of microbleeds
Complications, *n* (%)
Pericardial effusion requiring drainage
Pericardial effusion not requiring drainage
Transient ischemic attack
Cerebral infarction
Other thromboembolisms

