## DISCUSSION

4

The mechanisms of cerebral embolisms caused by the CA of AF are still under debate. Different technology‐, procedure‐, and patient‐related factors are considered to play roles in the multifactorial genesis of cerebral embolisms caused by CA of AF.^22^, ^23^ The potential embolic sources due to CA of AF are considered to be the development of thrombotic debris (clots and char) and air microbubbles, which are introduced or produced during CA procedures.^7^, ^24^ Haines et al.^24^ reported that both thrombotic debris and air microbubbles produced SCLs detected by MRI in a canine model.

Regarding the development of thrombotic debris (clots and char) during CA procedures, endothelial injury and tissue overheating, systemic activation of platelets and of the coagulation system, and debris introduced from within the transseptal sheath or catheter, may cause cerebral embolism.^22^, ^25^ Regarding the development of microbubbles during CA procedures, it has been reported that microbubbles can be introduced into the LA by a variety of mechanisms associated with introducing, withdrawing, and exchanging catheters within the transseptal sheath.^26^, ^27^

Some procedure‐ and patient‐related factors have been also reported as possible predictors of cerebral embolisms caused by CA of AF.^8^, ^27^, ^28^, ^29^ As procedure‐related factors, cardioversion during CA, lower ACT levels during CA, heparin application after the transseptal puncture, higher blood pressures during CA, type of oral anticoagulant, interrupted anticoagulation before CA, use of catheters with complex geometries, the LA dwell time, negative pressure in the LA caused by general anesthesia, use of RF energy during the transseptal puncture, additional linear LA lesions, and prolonged procedure time have been reported as risk factors of CA related embolisms, however, these relationships are controversial as well.^8^, ^27^, ^28^ As patient‐related factors, a history of a stroke or transient ischemic attack, higher CHADS_2_ and CHA_2_DS_2_‐VASc scores, male gender, hypertension, congestive heart failure, diabetes, coronary artery disease, PeAF, larger LA volume, spontaneous LAA echo contrast in preablation transesophageal echo, and LA scarring have also been reported as risk factors of CA related embolisms.^7^, ^30^, ^31^

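### The touch-up analysis in section 2.11 is worded backwards: it drops CB patients without touch-ups instead of those with RF touch-ups

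*Protocol article*

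**What the plan says.** Section 2.6.2 (CB ablation) makes touch-up part of the CB procedure: "When the CB ablation cannot achieve the PVI, additional focal ablation will be performed with a Freezor Max (Medtronic) or RF catheter".

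Section 2.11 (Statistical analysis) then sets an analysis rule for some of these patients. Its condition is "If RF catheters are used in the CB ablation group for touch‐ups", and the rule is to run analyses that "include both patients with touch‐ups and that excludes those without touch‐ups, respectively". The condition covers RF touch-ups only, although section 2.6.2 also allows a focal cryocatheter.

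Two other places bear on the point. Table 2 records "The need for touch‐up ablation" under the CB heading and has no counterpart under the RF heading. The basis of the main analysis is also given in section 2.11: "For the primary endpoint, safety analyses will be performed based on the intention‐to‐treat principle". A per-protocol analysis is added there as a supplement.

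**The concern.** An analysis that addresses RF use in the CB arm should set results with the touch-up patients beside results without them. The sentence removes the wrong group. Patients isolated by the balloon alone would be dropped, and the CB arm would consist of patients in whom the balloon did not achieve isolation and RF was added. That comparison answers no question the trial asks. An analysis plan that copied the sentence would inherit the error.

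The evident intention, excluding CB patients with RF touch-ups, is a reasonable supportive analysis but not a randomised comparison. Membership depends on what happened after randomisation, in one arm only. The article does not say how the result is to be read beside the main analysis. In an open-label trial it is better to settle both the rule and its standing before outcomes are known.

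**Working it through.** **1. The wording.** The three relevant statements, side by side:

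- Condition (section 2.11): an RF catheter was used for touch-up in a patient in the CB group.
- First analysis (section 2.11): touch-up patients are included.
- Second analysis (section 2.11): patients without touch-ups are excluded, so only touch-up patients remain.

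The closing word of the sentence signals two contrasting analyses. Read literally, both keep the touch-up patients and neither removes them. The contrast works only if the second analysis excludes patients with touch-ups.

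**2. What the literal rule would leave.** The arm size is 115 (section 2.8). The touch-up share t is not in the documents; 5% to 20% is assumed.

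- t = 5%: 115 × 0.05 = 5.75, about 6 CB patients
- t = 20%: 115 × 0.20 = 23 CB patients

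**3. Why the intended rule needs a caveat.** Section 2.6.2 triggers touch-up when the balloon cannot isolate the vein, which is known only after randomisation. Section 2.6.3 (RF ablation) defines no matching event, and Table 2 lists touch-up for CB only. Excluding on it therefore selects patients in one arm and leaves the other whole.

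**4. Possible size of a shift.** Let p be the overall CB rate of SCE, t the touch-up share and r the SCE rate in touch-up patients. The rate among the remaining CB patients is

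(p − t × r) / (1 − t)

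Section 2.8 assumes p = 20%. Both t and r are assumptions.

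- t = 10%, r = 35%: (0.20 − 0.035) / 0.90 = 18.3%, a shift of −1.7 points
- t = 5%, r = 30%: (0.20 − 0.015) / 0.95 = 19.5%, a shift of −0.5 points
- t = 20%, r = 50%: (0.20 − 0.10) / 0.80 = 12.5%, a shift of −7.5 points
- r = 20% at any t: the rate stays at 20%, no shift

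**5. Scale for comparison.** The stated sample size reproduces at a two-sided 5% level: (1.96 + 0.842)² × 2 × 0.20 × 0.80 / 0.15² = 111.6, so 112 per group. It does not depend on the touch-up rule. With 115 per group, RF at 20% and CB at 24.3%, the standard error is √(0.20 × 0.80/115 + 0.243 × 0.757/115) = 0.0547, and 1.96 × 0.0547 = 10.7 points. The 15-point margin therefore tolerates an observed CB excess of about 15 − 10.7 = 4.3 points. This only puts the shifts in step 4 in proportion; it does not mean that the touch-up analysis decides noninferiority.

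**The case against.** The strongest reply is that this is an editorial slip. The condition and the sentence structure make the intended contrast clear, few statisticians would run the literal version, and a detailed analysis plan is promised before database lock. That reply stands as to severity. It does not make the sentence right: it is a stated analysis rule, it says the opposite of its purpose, and it is the only version on view.

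The reply also has force on the intended form. Reporting results both with and without touch-up patients lets a reader see any change the exclusion causes, and isolating a balloon-only result is a sensible aim when RF energy has entered the CB arm.

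A reader might infer more: that the intended exclusion biases the trial towards noninferiority. The documents do not support that. The primary endpoint is analysed by intention-to-treat, which keeps touch-up patients in the CB arm. The touch-up sentence names no endpoint and is not tied to the noninferiority decision. The direction of any shift is also not established: the Discussion lists "use of catheters with complex geometries, the LA dwell time" among reported risk factors, but the same sentence calls these relationships controversial, and no SCE rate for touch-up patients is given.

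A reader might also infer that touch-up patients would be removed from the per-protocol set. Nothing in the article says so or treats touch-up as a deviation, so there is nothing to correct there.

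**Conclusion.** The wording error is certain: as written, the second analysis retains only CB patients who also received RF. The caution about the intended form is sound in principle, since it is a post-randomisation exclusion in one arm with no counterpart in the other. Its numerical effect is conditional. It lowers the apparent CB rate only if touch-up patients have more SCEs than other CB patients. The example of 20% falling to 18.3%, and the wider range of 0.5 to 7.5 points, rest entirely on assumed touch-up shares of 5% to 20% and assumed risks of 30% to 50%. With equal risk the shift is zero. The intention-to-treat conclusion does not move in any of these cases. The point is minor, but the sentence should be corrected.

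**What to change.** Reword the sentence in section 2.11 to: one analysis including and one excluding CB patients who received RF touch-ups. Add a second sentence stating that the exclusion analysis is supportive only and that noninferiority is judged on the intention-to-treat analysis, because touch-up arises after randomisation in the CB arm alone and the RF arm has no matching exclusion.

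Carry the same wording into the statistical analysis plan. The cost is two sentences, with no change to sample size, data collection or the primary analysis.

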### Study organization

2.12

The research group consists of investigators at a multicenter in Japan and an independent data monitoring committee. The Certified Review Board (CRB) and DSMB will regularly monitor the recruitment and conduct of the study, data quality, timeliness, distribution of the therapies within the trial groups, and serious AE related to the CA procedure.

### Ethics

2.13

The study is registered in the Japan Registry of Clinical Trials (jRCT) identifier (jRCT1052210013). The study is being conducted in accordance with the Declaration of Helsinki and the Ethical Guidelines for Clinical Studies issued by the Ministry of Health, Labour and Welfare, Japan. This study received approval from the CRB of the Osaka City University Hospital, Japan (OCU007E, April 6, 2021). A CRB‐approved informed consent form (written in accordance with the applicable laws for clinical research) will be obtained from every patient before study enrollment.

## RESULTS

3

The results of this study are currently under investigation.

## DISCUSSION

4

The mechanisms of cerebral embolisms caused by the CA of AF are still under debate. Different technology‐, procedure‐, and patient‐related factors are considered to play roles in the multifactorial genesis of cerebral embolisms caused by CA of AF.^22^, ^23^ The potential embolic sources due to CA of AF are considered to be the development of thrombotic debris (clots and char) and air microbubbles, which are introduced or produced during CA procedures.^7^, ^24^ Haines et al.^24^ reported that both thrombotic debris and air microbubbles produced SCLs detected by MRI in a canine model.

Regarding the development of thrombotic debris (clots and char) during CA procedures, endothelial injury and tissue overheating, systemic activation of platelets and of the coagulation system, and debris introduced from within the transseptal sheath or catheter, may cause cerebral embolism.^22^, ^25^ Regarding the development of microbubbles during CA procedures, it has been reported that microbubbles can be introduced into the LA by a variety of mechanisms associated with introducing, withdrawing, and exchanging catheters within the transseptal sheath.^26^, ^27^

Some procedure‐ and patient‐related factors have been also reported as possible predictors of cerebral embolisms caused by CA of AF.^8^, ^27^, ^28^, ^29^ As procedure‐related factors, cardioversion during CA, lower ACT levels during CA, heparin application after the transseptal puncture, higher blood pressures during CA, type of oral anticoagulant, interrupted anticoagulation before CA, use of catheters with complex geometries, the LA dwell time, negative pressure in the LA caused by general anesthesia, use of RF energy during the transseptal puncture, additional linear LA lesions, and prolonged procedure time have been reported as risk factors of CA related embolisms, however, these relationships are controversial as well.^8^, ^27^, ^28^ As patient‐related factors, a history of a stroke or transient ischemic attack, higher CHADS_2_ and CHA_2_DS_2_‐VASc scores, male gender, hypertension, congestive heart failure, diabetes, coronary artery disease, PeAF, larger LA volume, spontaneous LAA echo contrast in preablation transesophageal echo, and LA scarring have also been reported as risk factors of CA related embolisms.^7^, ^30^, ^31^

The pathogenesis of cerebral embolisms caused by the CA of AF is incompletely understood. Therefore, periprocedural monitoring is expected to be a useful approach to determine which part of the CA procedure is associated with MESs, although all MESs does not result in cerebral micro‐embolisms because of collateral circulation via the circle of Willis in the cerebral vasculature.^24^ TCD is an available method for real‐time monitoring of the embolic traffic in the brain. Miyazaki et al.^32^ used TCD throughout all CB ablation procedures in their observational study. They reported that a considerable number of MESs were recorded during a variety of steps throughout the procedure, and the total MES count/procedures reached over 500 per CA procedure.^32^ In this way, TCD is useful for real‐time monitoring during CA, however, monitoring throughout entire relatively long CA procedures such as RF ablation is hard to perform because TCD needs manual adjustment of the probe throughout the procedure. In this study, we will use a novel probe that will attach to the neck easily and be stable throughout the procedure, which will enable real‐time monitoring of the embolic traffic in both the CB and RF ablation groups. In addition to monitoring for MESs throughout the procedure and assessing how the CA procedure is associated with promoting MESs, we will assess the relationship between MESs during the CA procedure and cerebral embolisms detected by DWI‐MRI after the CA.^33^

Both CB and RF ablation is used worldwide, however, different technologies used for CA of AF have shown different characteristics of the complications.^34^ We will compare the incidence of cerebral embolisms caused by CA of AF between CB and RF ablation with the Embo‐Abl study.

## LIMITATIONS

5

We will not acquire brain MRI before CA in this study, and therefore, it is possible that postprocedural SCEs/SCLs may occur preprocedural. However, we think that is highly unlikely because acute cerebral lesions will be defined on 3 T DWI, which is positive only a few weeks after a cerebral embolism, and actually, acute cerebral lesions were found in none of the previous studies that assessed preprocedural MRI in patients who underwent CA of AF.^35^

## CONCLUSION

6

The Embo‐Abl study will be the first to compare the incidence of periprocedural cerebral embolisms caused by CA of AF between CB and RF ablation in a prospective, multicenter, randomized, controlled fashion.

## Data Availability

The data that support the findings of this study are available from the corresponding author upon reasonable request.
